### {#14 Sample size}

The power of these analyses depends on the proportion of participants receiving abdominal CT in each stratum. The abdominal CT proportions in the prior randomized controlled trial using these entry criteria were 52.4% and 54.6% in the two arms [28]. In estimating sample size, we chose a baseline abdominal CT proportion of 52.5%. A minimum clinically important difference of 5% was specified for the abdominal CT proportion (from an expected proportion of 52.5%). A difference of 5% (number needed to receive the FAST examination = 20) was chosen because 74% of physicians (162/180 pediatric emergency medicine physicians surveyed responded at 18 PECARN centers) were willing to perform at least 20 FAST examinations to avoid one abdominal CT. This includes 35% of physicians who reported no limit on the number of FAST examinations they would be willing to perform to safely decrease abdominal CT use.

Sample size modifications are required to adjust for interim analyses, although the increase is slight for conservative alpha-spending functions. We initially specified that a sample size of 3194 was needed to detect a 5-percentage point difference (for 80% power) using a four-group sequential analysis design. It subsequently became apparent during the initial enrollment period that the baseline CT proportion was lower (34%) and enrollment was higher than planned. Thus, we calculated a second sample size to detect a 4% difference in CT proportions which would still be meaningful.

We subsequently specified a four-stage group sequential design (with three interim analyses and one final analysis) with possible early stopping only to reject the null hypothesis in Statistical Analysis System (SAS) PROC SEQDESIGN and determined that a sample size of 4346 would provide a power of at least 80% for detecting the more difficult-to-detect 4% difference between groups in the proportion of CT use, which is when one group has 30% CT usage and the other has 34% CT usage. To permit replication, Figure 3 displays the SAS output from the PROC SEQDESIGN used to produce the sample size targets for the study design in our protocol.

**Fig. 3 Fig3:**
[figure not shown]
Sample Size Calculation in SAS

For those participants in the 0- to 3-year-old cohort, a 10% difference in abdominal CT proportions is clinically important. A 12% difference was found between arms in the single-center trial, but the sample size was too low to demonstrate statistical significance [28]. Assuming a baseline CT of 52.5% in all strata, a sample size of 796 participants in this age cohort would provide a power of at least 80% for detecting a 10% difference in the proportion of CT use between cohorts. Although a smaller difference may still be clinically meaningful, we are challenged by the feasibility of enrolling so many children in this age cohort.

We anticipate missed/delayed diagnoses of IAI to occur rarely. Among the 925 patients enrolled in our single-center FAST randomized controlled trial, only one missed/delayed diagnosis of IAI occurred (likely a false-positive CT and not a true missed IAI) [28]. Only 4 occurred in the PECARN observational study of 12,044 injured children [8]. Such outcomes are too infrequent to form a reliable basis for study sample size planning.

### {#15 Recruitment}

The study will enroll eligible patients as they present to the ED. Figure 4 provides the timeline for the study.

**Fig. 4 Fig4:**
[figure not shown]
Study Timeline

## Assignment of interventions: allocation

### {#16a Sequence generation}

Patients meeting enrollment criteria will be randomized to the FAST or no-FAST arms using computer-generated randomly permuted blocks by enrollment order (investigators will be masked to the order). In addition, randomization will be stratified by site and age cohort. These actions will ensure appropriate randomization, and that confounding variables (either known or unknown) are likely to be equally distributed between study arms.

### {#16b Concealment mechanism}

To ensure allocation concealment, sealed, opaque envelopes were shipped from the UC Davis Data Coordinating Center to all study sites. These envelopes are (1) readily available in the ED, (2) reveal the randomization assignment stratified by age cohort (younger than 3 years or 3 to 18 years old), and (3) contain the appropriate case report form. The sequentially numbered, sealed opaque enrollment packets are located near the ultrasound machine and are always available to the providers once eligibility is determined. Once opened, these packets will reveal study arm allocation and provide all pertinent case report forms.

### {#16c Implementation}

The allocation sequence was generated by the study statistician. Participants will be enrolled by trained research coordinators and clinicians providing care. PECARN studies have previously successfully conducted studies where treating clinicians themselves enroll eligible patients.

## Assignment of interventions: blinding

### {#17a Who will be blinded}

Treating physicians will not be blinded to the results of the FAST examinations. As the study evaluates provider actions (i.e., obtaining an abdominal CT) based on the FAST results, it would be inappropriate to blind the clinicians providing care. It would also be unethical to do so, as FAST results could potentially reduce harm to participants. Participants, by definition, will also not be blinded to study arm, but any potential bias from their knowledge that the FAST was performed should be minimal. Assessment of all outcomes will be performed by trained research coordinators blinded to study arm. All statistical analyses will be performed with the statistician blinded to study arm. After the statistical analysis is performed and reviewed with the study team, all results will be unblinded.

### {#17b Procedure for unblinding if needed}

Emergency unblinding of the intervention is unnecessary for this study as the clinicians will know if they provided a FAST examination.

## Data collection and management

### {#18a Plans for assessment and collection of outcomes}

We will follow the enrollment and data collection procedures which were proven highly successful in the prior single-center randomized controlled trial [28] and learned over two decades in PECARN. At the time of the patient’s arrival, the faculty ED physician and/or research coordinator will immediately evaluate and determine patient eligibility. As per ED protocol, each enrolled patient will undergo a complete trauma history and physical examination by the responsible faculty physician, and findings will be documented by that faculty physician on a standardized case report form. Although no laboratory tests are required by protocol, we will record the results of the hemoglobin/hematocrit, liver transaminases, lipase, and urinalysis (for blood), if obtained. Emergency department data will be collected using standardized case report forms.

### {#18b Plans to promote participant retention and complete follow-up}

Guardians of enrolled participants discharged from the ED will be contacted by text/telephone beginning 1 week after discharge from the ED visit for up to 3 months. Evidence from prior studies indicated missed IAIs manifest within 48h of injury [8, 28]. There is no specific retention plan for this study.

### {#19 Data management}

Data is entered into a REDCap database created by the UC Davis Data Coordinating Center. Research coordinators manually enter data from case report forms or directly from the electronic medical record when pertinent (radiology reports, laboratory values, laparotomy reports). Saved FAST examinations will also be uploaded into REDCap as previously described. Data entered into REDCap will undergo multiple levels of quality control to minimize errors. Built-in field validation (numeric ranges, date formats, and required fields) will be enabled at the time of entry to prevent implausible values. In addition, branching logic and calculated fields will be used to trigger immediate alerts when data are inconsistent or fall outside expected ranges. Standard REDCap data quality rules and custom queries will be run on a routine basis to identify outliers, missing data, and discrepancies. Regular data quality reports will be generated, reviewed, and documented, and anomalies will be resolved in a traceable manner. Missing data fields will prompt automated queries in REDCap. All case report forms will be retained for 10 years.

### {#27 Confidentiality}

To ensure patient confidentiality, the paper case report forms will be kept in a secure location per each site’s policy. All data entered into the REDCap database will be deidentified. The database will additionally be password-protected. UC Davis provides effective firewall hardware, automatic network intrusion detection, and the expertise of dedicated security experts to ensure database security.

### {#33 Plans for collection, laboratory evaluation, and storage of biological specimens for genetic or molecular analysis in this trial/future use}

No biological specimens are being collected or stored as part of this trial.

All analyses will account for site, sex, and age stratum differences. Baseline demographic (including age and sex), clinical and laboratory data, and outcome measures will be compared between the two cohorts (FAST versus the no-FAST study arms) using appropriate bivariable statistical methods to assess for parity between arms for known confounding variables (e.g., mechanism of injury, PECARN Abdominal Prediction Rule variables). Ninety-five percent CIs will be calculated for all measures of interest. All tests will be based on two-tailed alternatives. *P*-values < 0.05 will be considered statistically significant and adjusted for interim analyses. Categorical data will be compared using Cochran-Mantel–Haenszel risk difference testing and estimation method for stratified samples, using the Miettinen-Nurminen (score) confidence limits available in SAS for the common risk difference. McNemar chi-squared test will be used to compare differences in proportions between clinician suspicion of intra-abdominal injury before and after the FAST examination. Clinician suspicion will additionally be collapsed and compared into those with less than 1% suspicion and those with 1% or greater suspicion of IAI.

All continuous data will be assessed using nonparametric statistical analysis procedures for stratified data, with hypothesis testing using the Wilcoxon-Mann–Whitney procedure on outcomes that have been rank-aligned by stratum using the Hodges-Lehman estimator, a more powerful alternative to the van Elteren test [39]. ED length of stay and time to abdominal CT are continuous variables measured in minutes. We will compare ED and hospitalization lengths of stay between participants in the two study arms using nonparametric methods (described above). Hospitalization and laparotomy proportions are categorical variables (yes/no) and will be compared using methods described above for categorical variables.

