### {#10 Eligibility criteria}

Children up until their 18th birthday will be assessed for eligibility as (1) this is the age range evaluated by most pediatric EDs and the age range in the single-center randomized trial [28], and (2) mechanisms and injury responses are different in those older than 18 years. Inclusion and exclusion criteria are designed to enroll a hemodynamically stable population with approximately 5% having IAI. This is because a prior study suggests that use of the FAST examination safely decreases abdominal CT use in those children considered to have a 1 to 10% risk of IAI [31]. Furthermore, a meta-analysis of the FAST examination in injured children suggests that CT may be avoided in low-risk children with normal FAST examinations; however, the FAST should not be used to rule out injury in children at higher risk [30]. Inclusion and exclusion criteria follow the same criteria used in the prior single-center randomized controlled trial of FAST in children in which 5.4% had IAIs and are presented in Table 1 [28].

**Table 1 Tab1:** Inclusion and exclusion criteria

Inclusion criteria [28]:
• Blunt torso trauma from a significant mechanism of injury:
◦ Motor vehicle collision:> 60 mph, ejection, or rollover
◦ Automobile (>25 miles/hour) versus pedestrian/bicycle
◦ Falls greater than 20 feet in height
◦ Crush injury to the torso or assault to the abdomen
• Glasgow Coma Scale score of 9-14 with blunt torso trauma
• Blunt traumatic event with extremity paralysis or multiple long bone fractures, regardless of the mechanism
• History and physical examination suggestive of abdominal injury following blunt torso trauma of any mechanism
Exclusion criteria [28]: Patients will be excluded for:
• Age-adjusted hypotension
◦ Prehospital or initial emergency department age-based hypotension. [57]
• Initial Glasgow Coma Scale score of 8 or less
• Penetrating trauma: Patients who are victims of stab or gunshot wounds
• Traumatic injury occurring more than 24 hours prior to the time of presentation to the emergency department
• Transfer of the patient with an abdominal CT scan, FAST examination or laparotomy previously performed
• Patients with known disease processes resulting in intraperitoneal fluid including liver failure and the presence of ventriculoperitoneal shunts

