### {#12 Outcomes}

Primary outcomes will be measured and documented in both study arms. These outcome measures are the same as those used in the single-center randomized controlled trial. The primary outcomes are the abdominal CT proportion and the proportion of missed/delayed diagnosis of IAIs. The abdominal CT proportion will be calculated as the number of participants receiving abdominal CT scans in the initial 24 h divided by the number of participants in each arm (i.e., proportion of participants undergoing CT during their initial ED evaluation). Abdominal CT scans will be obtained at the discretion of the treating physicians in the ED. The other primary outcome is missed or delayed diagnosis of IAI. A missed diagnosis of IAI is defined as a diagnosis of IAI made after the patient is discharged from the hospital (if admitted) or from the ED (if not admitted to the hospital). A delayed diagnosis of IAI is defined as a diagnosis made after patient transfer from the ED to the hospital (including ward/intensive care unit bed). A delayed diagnosis may only be identified in a patient admitted to the hospital. Complications due to the missed/delayed diagnosis will be collected. We anticipate missed/delayed diagnoses to be rare but will nonetheless carefully assess for these as the FAST examination will require acceptance by clinicians that important injuries will not be missed if it is to be incorporated into practice.

Secondary outcome measures will also be collected and analyzed in both study arms. Although these outcomes are not the focus of the analysis, they will be gathered as they are important for assessing the utility of a pediatric trauma evaluation strategy using the FAST. Secondary outcomes include the following: (1) ED length of stay, (2) time to CT, (3) proportion of participants hospitalized and length of hospital stay, (4) proportion with abdominal CTs obtained in the subgroup of children 0 to 3 years old, (5) laparotomy proportion, and (6) physician suspicion of IAI.

ED length of stay is a continuous variable defined as the time (minutes) from ED arrival to ED disposition (ED discharge, hospital admission orders written, transfer to operating suite, or death). Abdominal CT time is defined as the start of the CT, and laparotomy time is defined as the time of entering the operating suite. Both of these are continuous variables and will be measured and compared as such. Time to CT or laparotomy will be measured from the time of ED arrival.

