The hospitalization proportion is the number of participants hospitalized in each study arm divided by the number of participants in each arm (proportion admitted to the hospital from the ED). Participants will be considered hospitalized if they meet any of the following: (1) Admitted to observation status, (2) admitted to the intensive care unit or ward, and (3) transported from the ED to the operating suite/interventional radiology. We will also measure the length of stay for those hospitalized. This will be a continuous variable measured in hours from the time of ED arrival to discharge from the hospital or death in the hospital.

The proportion of abdominal CT use in children 0 to 3 years old is the number of abdominal CT scans performed in each study arm divided by the number of participants in each arm (proportion of participants undergoing an abdominal CT during their initial ED evaluation) among the population 0 to 3 years old. Laparotomy proportion is a binary indicator for whether the patient underwent a laparotomy or laparoscopy to identify/repair an IAI.

In those participants who undergo the FAST examination, we will also measure the impact of the FAST on the clinicians’ subsequent assessments of risk of IAI. In all participants, regardless of randomization, we will ask if the clinician believes the patient should have an abdominal CT scan and will measure clinician suspicion of IAI (classified by the clinician as < 1%, 1 to 5%, 6–10%, 11–50%, and over 50%). In those who are randomized to the FAST examination, the clinician will, after the FAST examination, again document if they believe the patient should have an abdominal CT and their suspicion of IAI (with the same categories). Finally, the clinician will, after performing the FAST examination, document if the FAST changed their suspicion for IAI or plans for patient evaluation or management.

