A large, multicenter observational study in children with blunt abdominal trauma led by the study investigators demonstrated that FAST use at participating sites was highly variable (from 0.5% to 88% of patients) [31]. Use of the FAST, however, was associated with decreased CT use in those children considered to be at 1–5% or 6–10% risk of IAI prior to the FAST (relative risk of obtaining a CT compared to those without the FAST examination performed was 0.81 and 0.85, respectively) [31]. However, in a single-center randomized controlled trial of the FAST conducted by the study investigators, there was no difference in abdominal CT use in those who were randomized to the FAST versus no-FAST study arms [28]. Clinician suspicion of IAI, however, was significantly decreased in the FAST arm following FAST examination [28]. The decrease in clinician suspicion without a corresponding decrease in CT use in the FAST study arm may be a result of clinician awareness of the imperfect sensitivity of the FAST, particularly in injured children, or insufficient confidence in interpreting the images. It may also be a result of modifiable factors (training, confidence, etc.) that if intervened upon may safely reduce CT use.

We considered a cluster-randomized design at the level of the clinician, which could minimize the risk of intervention nonadherence. However, based on prior experience in our single-center trial in which crossover was rare, we anticipated low rates of nonadherence. Given the additional complexity of a cluster randomized trial, we determined that patient-level randomization remained the most efficient and scientifically rigorous approach. We acknowledge this as a potential limitation but expect a minimal impact on study integrity.

Missed or delayed diagnoses of IAIs are anticipated to be rare. Therefore, a feasible sample size to determine clinically important differences in the two arms in this outcome was not feasible. We chose to include it as a primary outcome, however, because clinicians need to be assured that use of FAST does not increase the frequency of missed IAIs or delay the diagnosis.

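### McNemar's test is assigned to a five-category ordered suspicion rating with no cut-point, and the change it tests exists only in the FAST arm although secondary outcomes are said to be analysed in both arms

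*Protocol article*

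**What the plan says.** The Outcomes section (item 12) has clinicians rate their suspicion of intra-abdominal injury in every participant, in five ordered bands: "classified by the clinician as < 1%, 1 to 5%, 6–10%, 11–50%, and over 50" (per cent). After the scan, clinicians of children in the FAST arm "again document if they believe the patient should have an abdominal CT and their suspicion of IAI (with the same categories"). The second rating is tied to that arm: "In those who are randomized to the FAST examination, the clinician will, after the FAST examination, again document".

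The statistical methods section (item 20a) gives the analysis: "McNemar chi-squared test will be used to compare differences in proportions between clinician suspicion of intra-abdominal injury before and after the FAST examination". The next sentence adds a binary version: "Clinician suspicion will additionally be collapsed and compared into those with less than 1% suspicion and those with 1% or greater suspicion of IAI".

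The Outcomes section introduces the whole list of secondary outcomes, with physician suspicion as the sixth item, by saying: "Secondary outcome measures will also be collected and analyzed in both study arms".

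**The concern.** The named test does not match the variable. McNemar's test in its ordinary form compares two paired proportions from a two-by-two table, and this rating has five ordered levels. The 1% split cannot be read back into the McNemar sentence, because the split is introduced as something extra. So the main analysis of the rating has a test but no cut-point, no stated extension to more than two categories, and no use of the order.

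This matters because the question has a direction. The article reports that suspicion fell after FAST in the earlier single-centre trial, and the natural result to report here is how far it falls. An analysis that ignores order can be highly significant without saying whether suspicion went down overall. The one dichotomy that is stated treats a move from 6–10% to 1–5% as no change.

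The lead-in about both arms is a separate difficulty. The comparison arm has no second rating, so the change cannot be analysed there. Under that lead-in, an uncontrolled before-after change could be taken for a randomised effect.

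**Working it through.** The article gives no effect size, power or number of participants for this outcome, so there is no stated figure to reproduce. The check uses assumed paired tables of 2173 children (4346/2, from the larger sample size and 1:1 allocation). The cell counts are invented, and all moves are of one category.

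**Formulas.** McNemar: (b − c)²/(b + c), with b and c the discordant counts. Bowker: the same term summed over all pairs of categories, with 5 × 4/2 = 10 degrees of freedom. Net percentage moving down: (d − u)/n, with standard error √[(d + u) − (d − u)²/n]/n, where d and u are the numbers moving down and up.

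**Table A: movement only between 6–10% and 1–5%.** 200 move down and 50 move up.
- Below 1% against 1% or more: 0 discordant pairs, so the test cannot be computed.
- Bowker: 150²/250 = 90.0 on 10 df, p about 5 × 10⁻¹⁵.
- McNemar for 1–5% against the rest, and for 6–10% against the rest: 90.0 each.
- Signed-rank test on category steps: z = 150/√250 = 9.49 (all steps equal one category, so all ranks are tied).
- Net moving down: 150/2173 = 6.9%. Standard error = √(250 − 22500/2173)/2173 = 15.48/2173 = 0.0071. The 95% CI is 5.5% to 8.3%.

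**Table B: the same counts between 1–5% and below 1%.**
- Below 1% against 1% or more: 150²/250 = 90.0. Falls out of the bottom of the 1–10% range are fully counted.
- Bowker is again 90.0.

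**Direction, category by category.** Start both tables with 800 children in the 1–5% band. In Table A the band grows from 800 to 950; in Table B it shrinks from 800 to 650. McNemar for that band is 90.0 both times, with opposite signs, although suspicion falls by the same net amount. The sign for a single middle category does not tell the reader which way suspicion moved.

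**Direction, symmetry test.** Take 100 down and 30 up between 6–10% and 1–5%, together with 30 down and 100 up between over 50% and 11–50%. Bowker = 70²/130 + 70²/130 = 37.7 + 37.7 = 75.4 on 10 df, far beyond p = 0.0001. In total 130 move down and 130 move up, so the net movement is zero.

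**Both arms.** The first rating is taken in all participants and the second only in those randomised to FAST. The planned test is before against after FAST, so it uses FAST-arm data alone. The second FAST-arm rating could be set against the only rating in the other arm, but the article does not plan this, and the two ratings would differ in timing as well as in allocation.

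**The case against.** A reader might infer that the 1% split is the only valid analysis on offer. The documents do not support that. The McNemar sentence speaks of proportions, which can be read as the proportion in each category before and after, and each of those is a valid paired comparison. Bowker's extension is valid too. Either would detect the shift in Table A, so the article's main analysis would not miss it.

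A reader might also infer that the split ignores movement throughout the range where FAST is expected to act. It does not: a fall from 1–5% or 6–10% to below 1% is counted. Nor does the rationale predict where suspicion will move. The Eligibility criteria section says of FAST that it "safely decreases abdominal CT use in those children considered to have a 1 to 10% risk of IAI", and the Discussion that its use was "associated with decreased CT use in those children considered to be at 1–5% or 6–10% risk of IAI prior to the FAST". Both concern CT use by risk before the scan, not change in suspicion.

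It can further be said that before and after proportions with confidence intervals show direction to the eye; that the article already describes the comparison as before and after FAST; that the both-arms phrase is a general lead-in and the first rating is indeed taken in both arms; and that an article may leave such detail to the analysis plan.

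Much of this stands, and it limits the point to a small one. It does not remove it. The article does not leave the test open: it names one whose ordinary form does not fit a five-level rating. Nothing in it claims a randomised effect on suspicion, but the lead-in is inaccurate for the change in this rating.

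**Conclusion.** The point holds in a narrow form. McNemar's test is attached to a five-category ordered rating without a dichotomy. The readings that make it workable are valid, but they discard the order and give no single directional result. The added 1% split does not count moves between 1–5% and 6–10%. The statement that secondary outcomes are analysed in both arms does not fit a change measured in the FAST arm alone.

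The size in practice is unknown, since it depends on how many children move between which bands; the tables above are assumptions that show the mechanism only. This is one secondary outcome. The primary analyses and the sample size are untouched, so it is a minor improvement and not a threat to the trial.

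**What to change.** For the five-category rating, name one paired test for ordered categories (Wilcoxon signed-rank, or an ordered test of marginal homogeneity), and report the net percentage moving down with its 95% CI. Keep McNemar for the split at 1% and for the yes/no judgement on whether the child should have a CT. Label the outcome as a before-after comparison within the FAST arm, and amend the lead-in to the secondary outcomes so that it no longer implies a both-arm analysis of this change.

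The cost is two or three sentences in the analysis plan. Both ratings are already collected, so no new data are needed, and the article describes enrolment as still under way, so the change can be made before the final analysis.
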